### Data analyses

#### Statistics

We will calculate descriptive statistics for the outcome measures comparing these by arm where it is sensible to do so. Risk differences with 95% confidence intervals will be calculated for binary outcomes such as cessation, and for continuous outcomes, such as reduction in cigarettes per day, we will calculate difference in means or difference in change in means. For the cessation and reduction outcomes, we will conduct an intention-to-treat analysis, where all randomized subjects will be included in the denominator. We will also conduct sensitivity analyses with different assumptions for missing data.

The data will be analysed by a multilevel model by examining diversion of smokers from cessation into reduction programmes by comparing uptake of cessation in the pharmacies prior to and during the reduction programmes with pharmacies providing a similar throughput of patients for cessation support but not selected to provide reduction programmes.

Health economic analyses are not required because extensive modelling of different formats of reduction programmes showed that each of these programmes are cost-effective by NHS standards and this was robust to changes in assumptions [3]. However, we will utilise our existing models of the cost-effectiveness of the programme by updating the estimates used in modelling by including these estimates derived from a naturalistic setting. The updated estimates will be used to set the sample size for a definitive trial.

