### Allocation to trial arms and treatment

#### Randomisation

Pharmacists will randomise smokers by sealed envelopes. Block randomisation stratified by pharmacy will be used with two blocks of 4 to ensure randomisation to each arm in every pharmacy that recruits at least 4 participants. Although blocks of 4 could become predictable, no pharmacist will recruit sufficient participants to discern the pattern. Telephonists conducting follow up will be blind to treatment allocation but this is an open label trial and participants and therapists will know which arm they are in.

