### Follow up procedures

We propose testing the feasibility of using a follow up method that is unlikely to be perceived by participants as providing them with behavioural support or enhance motivation to adhere. This will be by email/Webform emailed monthly for the 12 months of a participant's involvement in the trial. Monthly follow up will ensure that we can assess whether smokers have started their period of abstinence and schedule verification visits, based on a process outlined for trials of this kind [18]. Web follow up has achieved > 90% follow up in a previous trial [19]. Based on our experience of trials in smokers' clinics, most patients have email addresses and these are useful for follow up. Text reminders will be sent to participants registered for email follow up not responding to the email. For those not using a computer regularly, phone follow up by telephonists will be used so that the pharmacist/therapist is not conducting follow up.

Sustained smoking reduction will be measured as self-reported daily cigarette consumption at 12 month follow up, with a reduction being counted as self-reported consumption lower than at baseline. Sustained reduction will be counted as achieved if during the last four months (i.e. reports at month 9-12) of follow up, a person is smoking less at every follow up occasion than at baseline, measured by self-report. If a monthly report is missing, a person will be counted as having achieved sustained reduction if all other reports show this is the case and the last report is not missing. If two reports are missing, a person will be counted as not having achieved sustained reduction. Mean cigarettes per day at the end of follow up will be calculated from the last follow up only. If cigarettes per day is missing, then this will be replaced by baseline cigarettes per day, but in sensitivity analysis, we will use last observation carried forward.

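### Cigarettes per day: the plan leaves two estimators open, and neither is as precise as adjusting for the baseline consumption it already collects

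*Protocol article*

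**What the plan says.** The Statistics section of the protocol article frames the arm comparisons as descriptive: "We will calculate descriptive statistics for the outcome measures comparing these by arm where it is sensible to do so". For continuous outcomes, with a fall in daily cigarettes as its example, it states that "we will calculate difference in means or difference in change in means". For binary outcomes it states: "Risk differences with 95% confidence intervals will be calculated for binary outcomes such as cessation".

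Other sections bear on which continuous estimator is meant. Trial Outcomes lists average consumption when the trial ends. Follow up procedures says "Mean cigarettes per day at the end of follow up will be calculated from the last follow up only", with a missing value filled by the participant's baseline value and last observation carried forward as a sensitivity analysis.

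On the design, the Randomisation section says "Block randomisation stratified by pharmacy will be used". The only model named in the Statistics section is for a different question: "The data will be analysed by a multilevel model by examining diversion of smokers from cessation into reduction programmes". No baseline covariate or pharmacy term is named for the arm comparisons.

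**The concern.** The phrase for continuous outcomes does specify a method, but it specifies two and gives no rule for choosing. A final-value difference and a change-score difference estimate the same effect under randomisation, yet in any one trial they give different numbers. Which is the more precise depends on a correlation that is unknown in advance. Without a rule, the choice can be made after both results are visible.

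This outcome is not peripheral. Primary objectives 2 and 3 compare the programmes on smoking reduction as well as on cessation. The Statistics section also says that estimates updated from this trial will set the sample size of the definitive trial. Baseline consumption is recorded in any case, because the reduction definitions and the missing-value rule depend on it, so the more precise analysis needs no further data.

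A smaller matter goes with it. Allocation is blocked within pharmacy, and an analysis that leaves pharmacy out gives intervals slightly wider than the design warrants.

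**Working it through.** **Inputs.** From the protocol article: 160 participants in 10 pharmacies (Sample size); about 80 per level of each factor (Figure 1 caption); 95% confidence (Statistics, stated there for risk differences and used here for means). Assumed, because the documents give neither: baseline to month-12 correlation r = 0.3, 0.5, 0.7, and pharmacy ICC = 0.01, 0.05, 0.10. Equal SDs at baseline and month 12 are also assumed. The plan gives no precision figure for cigarettes per day, so there is none to reproduce. Table 1 concerns abstinence and is not used.

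**1. How far the two permitted estimates can differ.** With the same people in both analyses (the baseline fill for missing values ensures this),

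change-score difference = final-value difference − baseline difference.

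The gap is therefore the chance baseline imbalance. Its standard error is √(2/80) = 0.158 baseline SD, so in 95% of trials it lies within ±1.96 × 0.158 = ±0.310 SD. With equal SDs, that equals the 95% half-width of the final-value comparison itself. This step needs no value of r.

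**2. Precision.** In units of the outcome variance, the relative variances are: final value 1; change score 2(1 − r); baseline-adjusted 1 − r² (large-sample). The 95% half-width at 80 versus 80 is 1.96 × √(2v/80), where v is the relative variance.

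| r | Variance: final / change / adjusted | Half-width (SD): final / change / adjusted | Cut v. better stated estimator | Cut v. worse stated estimator |
|---|---|---|---|---|
| 0.3 | 1 / 1.40 / 0.91 | 0.310 / 0.367 / 0.296 | 1 − 0.91/1 = 9% | 1 − 0.91/1.40 = 35% |
| 0.5 | 1 / 1.00 / 0.75 | 0.310 / 0.310 / 0.268 | 1 − 0.75/1 = 25% | 25% |
| 0.7 | 1 / 0.60 / 0.51 | 0.310 / 0.240 / 0.221 | 1 − 0.51/0.60 = 15% | 1 − 0.51/1 = 49% |

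Against the better stated estimator, the equivalent group sizes are 80/0.91 ≈ 88, 80/0.75 ≈ 107 and 80 × 0.60/0.51 ≈ 94, in place of 80. The final value beats the change score below r = 0.5 and loses to it above. The baseline-adjusted estimate is at least as precise as both for r between 0 and 1. Because missing values are filled with baseline, r will also depend on dropout, which is a further reason why neither stated estimator can be picked in advance as the better one.

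**3. Pharmacy.** Leaving out a balanced stratum inflates the interval by 1/√(1 − ICC): 1.005, 1.026 and 1.054 at ICC 0.01, 0.05 and 0.10. Equivalently, including it narrows the interval by 1 − √(1 − ICC) = 0.5%, 2.5% and 5.1%. A simulation of 10 pharmacies × 16 participants, balanced within pharmacy (4,000 runs per setting), agrees. At ICC 0.10 the unadjusted final-value test had type I error of about 3.5–4.3%, and the baseline-adjusted model with pharmacy about 4.7–5.1% (Monte Carlo SE about 0.3 points). Once baseline is in the model, adding pharmacy hardly moves the actual SE (0.1281 without, 0.1279 with, at ICC 0.10 and r = 0.5).

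**4. Limits of stratifying the risk differences.** Strata formed by pharmacy and the other factor number 10 × 2 = 20, with 160/20 = 8 people each, or 4 versus 4 at full recruitment. The Qualitative process evaluation section allows for pharmacists who recruit few or no participants. A stratum with only one arm contributes nothing to a Mantel-Haenszel risk difference, which conflicts with the Statistics section's rule of keeping everyone randomised in the denominator.

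**The case against.** The strongest reply is that this is a pilot. The comparisons are labelled descriptive, the sample was chosen for feasibility, and the main efficacy outcome is four-week abstinence, which is binary. The large variance gains concern cigarettes per day only. The wording on continuous outcomes is generic, and the outcome sections lean towards the final value. All of this stands and limits the consequence. It does not remove the ambiguity, because the Statistics section's own example is a reduction, which points to change. The disclaimer about power in the Sample size section concerns abstinence, not the choice of estimator for consumption.

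Four stronger readings are tempting, and the documents do not support them.

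- *The plan ignores baseline consumption.* It does not. A change score subtracts it, and baseline also enters the 50% threshold, the definition of sustained reduction and the missing-value rule. What is absent is baseline as a covariate.
- *The risk differences are unadjusted and unstratified.* The article does not say so. That would be inferred from silence in a condensed text, and a full protocol or analysis plan may supply the detail.
- *Adjustment is worth about a third more patients.* That figure (1/0.75 = 1.33) is the peak, at r = 0.5. Against the better stated estimator the gain is about 10% at r = 0.3 (1/0.91) and 18% at r = 0.7 (0.60/0.51).
- *Omitting pharmacy biases the results.* It does not. It makes intervals slightly conservative.

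**Conclusion.** The point holds for the continuous outcome. The stated method allows two estimators that can differ by up to about 0.31 SD through chance imbalance (95% range, 80 versus 80), and nothing else in the article settles which applies. A baseline-adjusted analysis removes the choice and cuts variance by about 9–25% against the better stated estimator for r between 0.3 and 0.7, and by up to 49% against the worse. These percentages rest on assumed correlations and equal SDs. The existence of two estimators, and the size of the gap between the final-value and change-score estimates in baseline SD units, do not.

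The pharmacy point is minor: about 0.5–5% of interval width over the assumed ICC range, and close to nothing in actual precision once baseline is in the model. It would not justify a change on its own. A reader might infer that the choice is meant to be made after seeing the data. The documents show only that it is left open.

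**What to change.** In the Statistics section, replace the phrase for continuous outcomes with one pre-specified estimator. Suggested wording: *Cigarettes per day at month 12 will be analysed by a linear model with both randomised factors, baseline cigarettes per day and pharmacy (the randomisation stratum) as terms; adjusted mean differences with 95% confidence intervals will be reported for each factor.* The existing missing-value rule and its last-observation sensitivity analysis can be run through the same model. The text should say whether pharmacy enters as a fixed factor or a random intercept.

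As an accompanying clarification, say how risk differences for binary outcomes account for pharmacy. Either stratify on pharmacy with small pharmacies pooled by a rule set in advance, or use a model-based standardised risk difference that keeps all randomised participants. Avoid strata formed by pharmacy and the other factor, for the reason given in step 4.

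The cost is a few sentences of analysis text. Baseline consumption and pharmacy are already recorded. With pharmacy fixed, the linear model uses 1 + 2 + 1 + 9 = 13 parameters and leaves 160 − 13 = 147 residual degrees of freedom, so the loss from the extra terms is negligible.

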## Methods/Design

### Participant Recruitment

Pharmacists who work for NHS stop smoking services will be recruited from areas of high smoking prevalence in Birmingham and Yorkshire region; those treating at least four new smokers for cessation per month will be eligible. Over 60 pharmacists in Birmingham see this many patients in the NHS stop smoking service and most are recruited by brief interventions across the counter, thus providing a naturalistic setting in which to test the implementation of reduction programmes and integration with other smoking cessation efforts.

We plan to recruit 10 pharmacies and for each to recruit four participants into a reduction programme each month, providing a quota of 16 in four months. We plan two waves of recruitment. Using two waves will allow us to learn lessons from the first wave, which is consistent with the developmental nature of this trial.

Educational outreach visits are effective in changing GP's behaviour [10]. We will make visits to local GPs to inform them about the programme and encourage them to refer reluctant quitters to the reduction programme. GPs will be given referral cards for their local pharmacy provider to give to patients. If the recruitment of participants is particularly slow during the either wave, GP's will be asked to send a letter to their registered current smokers. The letter will inform them that the reduction programme is available at their local pharmacy. It will also give details of how they can take part, should they want to, along with an information leaflet about the study.

Pharmacists will be asked to recruit participants opportunistically as well as receiving referrals from GPs. To assist opportunistic recruitment, pharmacists will display a poster in the window. Pharmacists will be compensated for their time with service support funding.

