### Sample size

This is a pilot trial designed to test the processes, examine implementation issues, and reactions to the programme of those involved. We estimated a sample size of 160 participants recruited in 10 pharmacies would be sufficient to test the feasibility of the study. The outcomes therefore include the percentage of pharmacists that agree to participate, the percentage that are trained, the percentage that actually recruit smokers into reduction programmes. Our most important efficacy outcome (because it is linked with unequivocal health benefits) is smoking cessation. We will record the weekly recruitment rate of patients into the reduction programmes and into NHS stop smoking programmes, comparing the rate of recruitment into stop smoking programmes for pharmacists participating in the trial with those not doing so. This will give evidence on whether smokers are being diverted by reduction. For smokers in each type of programme, we will record the number of contacts made, the time of the pharmacist used in delivering the programmes, the amount of NRT used in each arm, the number of people that try to quit, and the number of people that attend the pharmacist for post-cessation support as a proportion of those that try to quit. We will measure the fidelity to each programme by recording some consultations and analysing their content against the schedule of proposed content. We will record sustained smoking reduction and abstinence, although the trial is not powered to detect worthwhile differences in the abstinence outcomes. Four week and six month abstinence rates will be measured following the Russell standard. We will record the proportion of people that complete the webform/telephone follow up.

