### Transferring to the cessation programme

The aim of the reduction programme is to help people reduce and pharmacists will be encouraged not to pressure people to stop smoking, while explaining that proven health benefits derive from smoking cessation rather than reduction. However, most people who want to reduce smoking want to do so as a way of stopping [16,17], though rarely with a predetermined timetable. It is for the therapist and the patient to determine whether and when a person is transferred to the cessation programme. Pointers towards possible cessation are:

• Increased confidence that the patient can control her/his smoking.

• Cigarette consumption has fallen to five per day or fewer, or the person is going most of the day without smoking.

Participants in the No-support arms will be asked about their quitting attempt when they return to the pharmacy for more NRT. A key principle of the whole reduction approach is that failed quit attempts do not lead to an end of the programme. If a person moves to cessation and the quit attempts fails, they can resume the reduction programme and continue to control their smoking until they are ready to stop again.

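### The diversion comparison does not exclude reduction participants who later transfer to cessation; if they are registered as new cessation clients, it is biased towards finding no diversion

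*Protocol article*

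**What the plan says.** The Statistics section (under Data analyses) plans a multilevel model "examining diversion of smokers from cessation into reduction programmes". It does this by "comparing uptake of cessation in the pharmacies prior to and during the reduction programmes with pharmacies providing a similar throughput of patients" that were not selected to offer reduction. The Sample size section describes the same measure more briefly, as "comparing the rate of recruitment into stop smoking programmes for pharmacists participating in the trial with those not doing so", and states the inference to be drawn: "This will give evidence on whether smokers are being diverted by reduction". The Trial Outcomes section repeats that comparison. None of the three places says whether a person already enrolled in the reduction trial can also count as cessation uptake.

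The section on transferring to the cessation programme sets up movement from reduction to cessation: "It is for the therapist and the patient to determine whether and when a person is transferred to the cessation programme". It expects this movement, since "most people who want to reduce smoking want to do so as a way of stopping". It also allows repeats, because after a failed quit attempt participants are told that "they can resume the reduction programme and continue to control their smoking until they are ready to stop again". The Supported short programme section aims at cessation by week 4, or by week 8 if that fails. Secondary objective 3 treats referral from reduction to cessation, and quitting afterwards, as a quantity to estimate.

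**The concern.** Diversion concerns a smoker's first choice: someone who would have entered cessation enters reduction instead. It lowers the number of smokers entering cessation directly. Transfers run the other way. They can occur only in pharmacies that offer reduction and only once the programme has started, which is exactly the combination that a before/during, trial/control contrast isolates. A secular trend would cancel in that contrast; transfers would not.

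If transfers are counted, the quantity estimated is transfers minus diverted smokers, not diversion. The bias always runs towards no diversion, and it grows as the reduction programme moves more people on to quitting. The Background section names diversion as the main concern behind guidance that did not recommend reduction programmes, so a falsely reassuring result would weaken the pilot on that question.

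**Working it through.** The protocol gives no sample size, power or effect size for the diversion analysis, so there is no stated figure to reproduce. The check is a count identity.

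**Inputs from the protocol**
- Cessation throughput: "those treating at least four new smokers for cessation per month will be eligible" (Participant Recruitment). At that minimum, a pharmacy sees 4 × 4 = 16 cessation clients in 4 months, and 10 pharmacies see B = 160.
- Reduction recruits: a quota of 16 per pharmacy in 4 months, so R = 160 over 10 pharmacies.

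**Assumed, because the protocol gives no value**
- d, the share of reduction recruits who would otherwise have entered cessation: 25%, with 10% and 50% as a range.
- t, the share of reduction recruits who transfer within the counted window and are registered as new cessation clients: 21% and 35.7%. These are borrowed from the Sample size section and Table 1, where they are 4-week abstinence proportions. They are not transfer rates and serve only as plausible values.
- No change in control pharmacies, and each transfer counted once.

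**Formula**

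True change in direct cessation entries = -d × R/B.

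Apparent change with transfers counted = (t - d) × R/B.

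**Results**

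| Scenario | True change | t | Apparent change |
|---|---|---|---|
| R/B = 1, d = 25% | -25% | 0% (transfers removed) | -25% |
| same | -25% | 21% | 21 - 25 = -4% |
| same | -25% | 25% | 25 - 25 = 0% |
| same | -25% | 35.7% | 35.7 - 25 = +10.7% |
| R/B = 1, d = 25%, only the short-programme half transfers in the window | -25% | 21% of that half | 0.5 × 21 - 25 = -14.5% |
| same | -25% | 35.7% of that half | 0.5 × 35.7 - 25 = -7.15% |
| R/B = 1, d = 10% | -10% | 21% | 21 - 10 = +11% |
| R/B = 1, d = 50% | -50% | 21% | 21 - 50 = -29% |
| Twice the throughput (B = 320), d = 25% | -12.5% | 21% | 0.5 × (21 - 25) = -2% |
| same | -12.5% | 35.7% | 0.5 × (35.7 - 25) = +5.35% |

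**Longer window.** If the counted period is the 34 weeks of the standard programme, about 7.8 months, the minimum throughput is about 31 clients per pharmacy instead of 16. Each 10% of the 16 reducers who transfer (1.6 people) then adds 1.6/31, about 5%, instead of 1.6/16 = 10%. A diversion of 4 people is likewise about 4/31 = 13%, instead of 4/16 = 25%.

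**What does not depend on the assumptions.** If transfers are counted, the shift is upwards for every t above zero. Masking is complete whenever transfers counted in the window at least equal the diverted smokers, whatever the throughput. Repeat entries by one person would add to the shift.

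**The case against.** The strongest reply is that nothing in the article says transfers are counted. The wording can be read as two separate entry streams. The Sample size and Trial Outcomes sections speak of recruitment into each type of programme, Participant Recruitment measures throughput in new smokers, and reducers who move on are described as transferred, with the option to resume reduction. The Sample size section also records quit attempts and post-cessation attendance for each type of programme, so reducers who quit may be tracked within their own programme. A counting rule could sit in the full protocol or analysis plan. This stands as far as it goes: a reader might infer that the analysis does count transfers and will hide diversion, and the documents do not support that. They leave the matter open. But the article states the comparison three times, says what will be inferred from it, and describes a transfer into a cessation programme without keeping the two apart. The measure as worded admits the biased reading.

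The second reply concerns size. A reader might infer from the quota and the eligibility minimum that every 10% of reducers who transfer offsets 10% of throughput, or that diversion would disappear. That needs the minimum throughput, all transfers inside 4 months, and, for exact cancellation, equal transfer and diversion rates. The protocol supports none of these as expectations. Support in the standard programme runs to 34 weeks, so many of its transfers may fall outside a 4-month window. In the short-programme-only scenarios at 21% and 35.7%, the diversion is attenuated but still visible.

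Third, a reader might take the Sample size and Trial Outcomes wording, which mentions no pre-period, as a rival analysis. It is better read as a shorter description of the comparison in the Statistics section.

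Finally, diversion is one process measure in a feasibility pilot, and the article ties no decision rule to it. That limits the consequence but does not remove the ambiguity. Total uptake including transfers is a legitimate measure of the net effect on cessation; it answers a different question from diversion.

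**Conclusion.** The point holds conditionally. The diversion outcome, as worded, does not exclude reduction participants who later transfer to cessation, and the article does not say whether they are registered as new cessation recruits. If they are, the contrast is biased towards no diversion, and neither the control pharmacies nor the pre-period corrects it. The direction is certain under that condition. The size is not, because it rests on assumed transfer and diversion rates, on throughput at the eligibility minimum and on a 4-month window. Under those assumptions, the illustration runs from modest attenuation of a 25% fall to complete masking or an apparent rise. The documents do not establish that the analysis will conceal diversion. They leave open a reading under which it could.

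**What to change.** In the Statistics section, define the diversion outcome as new cessation clients at the pharmacy who were never enrolled in the reduction trial, counting each person once. State the calendar period that counts as during the programme. Report transfers from reduction to cessation separately, and show total uptake including transfers as a secondary measure of the net effect on cessation. Refer to this definition in the Sample size and Trial Outcomes sections. Who may transfer, and when, stays as it is.

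The cost is a flag on the trial pharmacies' cessation counts to identify trial participants. Trial enrolment is known, and quit attempts and post-cessation attendance are already to be recorded. The flag should be in place before the pharmacy counts are extracted.
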